#### Coach-Based MEI for Youth Living With HIV

The second aim of the protocol is an RCT to examine the efficacy of a mobile-enhanced coach-based intervention to achieve sustained retention and engagement in HIV care among youth living with HIV who are not virally suppressed.

#### Aim 2

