At the core of the coached-based MEI approach are supportive services such as navigation, adherence counseling, and tailored support for care engagement and treatment adherence for persons living with HIV. This intervention focuses on 3 steps in the support process: MyCare (steps 1 and 2) and MyHealth (step 3). Participants who are living with HIV start with MyCare (step 1) to support the decision to (re-)initiate HIV care. This includes the use of MI to help orient the client toward seeking and initiating care. MyCare (step 1), which is modeled after life steps, a single-session intervention grounded in cognitive-behavioral principles, is at the core of several successful ART adherence interventions [12,87,88]. MyCare (step 2) adds to this evidence-based approach by recognizing that adherence to medications is a personal choice grounded in a variety of behavioral and psychosocial domains. MyHealth (step 3) is based on the premise that a patient engaged in self-management and supportive strategies will feel empowered to take ownership of their own health care needs.

The face-to-face visits consequently address psycho-education about HIV risk, HIV and ART, planning and problem-solving to access and maintain a steady supply of medication, formulating a daily medication schedule, cues for pill-taking, coping with side effects and/or other participant concerns, developing a plan to mitigate side effects and responses to slips in adherence (if applicable), and engaging around condom use and/or limiting sexual risk behaviors. Counseling is tailored to the participants’ specific needs and case management or navigation needed.

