The PUSH study uses a built-in randomization engine adapted from previous studies [89]. The allocation between intervention and control arms is determined randomly by the engine, where each round comprises 2 intervention and 2 control assignments that are linked to the stratification factors of site and age group. Once a round is completed, a new round begins.

Participants are asked to participate in research visits at 0, 3, 6, 9, 12, and 18 months (exit interview). This visit schedule aims to ensure frequent contact and to minimize attrition. Laboratories and study-related activities are described in Table 2. Surveys provided at baseline (Textbox 1) are re-administered at each follow-up with additional questions focused on ART, PrEP, barriers, and facilitators to adherence.

**Table 2 table2:** Study visits and associated laboratory tests.

Tasks	Visits					
	Baseline	3 months	6 months	9 months^a^	12 months	18 months
Complete a survey	✓^b^	✓	✓	✓	✓	Exit interview
Provide blood for HIV-1 RNA viral load testing (aim 2) or HIV-1 antibody testing (aim 3)	✓	✓	✓	—^c^	✓	—
Provide urine for drug testing	✓	✓	✓	—	✓	—
Update locator information	✓	✓	✓	✓	✓	—
Meet with MEI^d^ coach (intervention only)	✓	✓	✓	✓	✓	✓
Medical chart review (research staff only)	✓	✓	✓	✓	✓	✓
Compensation, US $	50	50	50	10 check-in via phone; 25 survey	50	25
Participate in an in-depth interview (selected participants)	✓	—	✓	—	✓	—
Compensation, US $	25	—	25	—	25	—

^a^9-month visit constitutes either a brief phone check-in (5 min) or in-person survey (15 min).

^b^Data collected at this time point.

^c^Data not collected at this time point.

^d^MEI: mobile-enhanced intervention.

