#### Data Analysis

Aim 1 analyses are descriptive and include baseline characteristics related to sociodemographic characteristics, HIV infection, and sexual behavior of the YBLMSM and YBLTW samples across all sites as well as stratified by site. Descriptive tables with unweighted estimates and Pearson chi-squared tests for significance are used to compare age, web-use and venue attendance, and other characteristics of each recruited seed type.

To compare the efficiency of *seeds* from direct versus indirect seed selection in the recruitment of HIV-positive or at-risk youth, we use the RDS statistical package developed by Schonlau and Liebau [90]. This permits an assessment of the overlap of networks across seed types and across recruitment sites. Efficiency is assessed through recruitment diagnostics, including coupon return rate, homophily, the mean number of recruits, and recruitment depth per seed type. This approach also allows us to assess the time from recruitment activation through the achievement of target sample size and response rates. RDS weights will not be utilized in these analyses, as this aim focuses on descriptive sample proportions rather than producing population-based estimates. We will also examine the networks described by younger (aged 15-19 years) and older (aged 20-24 years) participants recruited from different *seeds* and use similar methods to understand the overlap of age groups across different networks.

The primary outcome for aim 2 is durable viral suppression (HIV viral load<200 copies/mL), and the secondary outcome is retention in HIV care (defined as documented 2 or more follow-up medical visits over 12 months, treated as a dichotomous variable). The primary outcome for aim 3 is self-reported PrEP use over 12 months in PrEP users, and the secondary outcome is self-reported condom use in PrEP nonusers. The overall approach is based on an intention-to-treat analysis with treatment assignment (eg, coached-based MEI vs SOC) being the primary independent variable for all models.

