The success of the randomization process is measured by comparing the distribution of participant characteristics between the 2 groups at baseline. If the randomization process does not result in comparable groups, adjustment is made for group differences in the multivariable models. For aim 2, logistic regression is used to examine whether participants who receive MEI coach are more likely to be virally suppressed as well as retained and engaged in HIV care than participants in the SOC arm. Generalized estimating equations (GEE) are used to determine whether treatment assignment predicts differences in retention for the coached-based MEI versus the SOC groups using repeated measurements over a 12-month period. GEE is used for the longitudinal data as it adjusts for the intra-personal correlation of repeated measurements on the same individual and provides an estimate of the standard error that is robust to misspecification of this correlation structure.

For aim 3, to evaluate whether YBLMSM and YBLTW receiving coached-based MEI have greater uptake of PrEP over 12-months, a survival model is used to examine whether intervention assignment is associated with time to PrEP use. GEE is used to determine whether treatment assignment predicts differences in PrEP utilization and adherence over time for the coached-based MEI versus SOC groups using the repeated measures over the 12-month period [91]. For both aims, we explore trends in uptake and adherence to treatment or PrEP for the intervention group compared with the control group by including an interaction term between time from randomization and treatment assignment.

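### Aim 2's retention outcome is one yes/no value per person with no visit spacing, so the planned repeated-measures GEE has nothing to repeat and two early visits count as sustained retention

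*Protocol article*

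**What the plan says.** The objective of the aim 2 trial (Coach-Based MEI for Youth Living With HIV) is "to achieve sustained retention and engagement in HIV care among youth living with HIV who are not virally suppressed".

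In Data Analysis the primary outcome is durable viral suppression. The secondary one reads: "retention in HIV care (defined as documented 2 or more follow-up medical visits over 12 months, treated as a dichotomous variable". No minimum gap between visits, and no requirement for a visit in each part of the year, is given.

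The same section then states two analyses of retention:

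- Logistic regression, which also covers engagement in care and compares with SOC: "logistic regression is used to examine whether participants who receive MEI coach are more likely to be virally suppressed as well as retained".
- GEE, for this question: "treatment assignment predicts differences in retention for the coached-based MEI versus the SOC groups using repeated measurements over a 12-month period". The reason given for GEE is the correlation among repeated measurements on the same person.

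A time-by-arm interaction appears later in the section, but for other outcomes: "we explore trends in uptake and adherence to treatment or PrEP for the intervention group compared with the control group".

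Table 2 lists "Medical chart review (research staff only") at baseline and at 3, 6, 9, 12 and 18 months. No retention variable per interval is derived from it.

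**The concern.** There are two linked problems.

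First, the outcome and one of its models do not fit. A count of visits over 12 months, cut at two, exists once per participant. A repeated-measures GEE needs an outcome that exists several times. Either the GEE duplicates the logistic regression, or it uses a second retention variable that the article does not define and whose intervals could be chosen after results are seen.

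Second, the definition does not capture what the aim names. Without spacing, two visits in the first weeks and none afterwards count as retained. An effect confined to early visits is plausible for this intervention, because "Participants who are living with HIV start with MyCare (step 1) to support the decision to (re-)initiate HIV care".

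Retention is a secondary outcome, but it is the only stated outcome that measures the retention named in the aim. The logistic regression could favor MEI when the arms differ only in early attendance. The analysis that could show whether the difference fades has no outcome to work on.

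**Working it through.** **Fit of outcome and model.** The article gives no rate, power or sample size for retention, so there is no stated figure to reproduce. As a check, one binary record per person (204 people, with 50% versus 65% retained assumed for illustration) was analysed both ways. Logistic regression with robust standard errors and logistic GEE gave the same log odds ratio (0.620) and standard error (0.290). With clusters of size one, the GEE adds nothing.

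**How the rule treats people who leave care.** Assumption: visits while in care are Poisson, one every 1 to 3 months. With mean count mu, P(2 or more visits) = 1 − exp(−mu)(1 + mu).

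| Leaves care at | Visit every 3 months | Every 2 months | Every month |
|---|---|---|---|
| Month 3 | mu = 1: 0.264 | mu = 1.5: 0.442 | mu = 3: 0.801 |
| Month 6 | mu = 2: 0.594 | mu = 3: 0.801 | mu = 6: 0.983 |

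A quarterly attender in care all year has mu = 4 and P = 0.908.

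**Arm contrast.** From Sample Size Considerations: 102 analysable per arm. Assumed: quarterly visits; 50% in care all year in both arms; 20% (SOC) versus 30% or 40% (MEI) in care only to month 6; the rest never in care. The test is a two-sided 5% pooled z-test, enumerated exactly.

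Stated outcome:

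- SOC: 0.5 × 0.908 + 0.2 × 0.594 = 0.573
- MEI at 30%: 0.5 × 0.908 + 0.3 × 0.594 = 0.632, significant in 14.6% of trials
- MEI at 40%: 0.5 × 0.908 + 0.4 × 0.594 = 0.692, significant in 42.4% of trials

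A visit in both half-years:

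- In care all year: (1 − exp(−2))² = 0.748
- Leavers at month 6: 0
- Each arm: 0.5 × 0.748 = 0.374, significant in 5.1% of trials

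**Later departure (40% versus 20%).** A leaver at month L has mu = L/3 under the stated rule. Under the both-halves rule the probability is (1 − exp(−2))(1 − exp(−(L − 6)/3)).

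| Leaves at month | Stated outcome significant | Both halves significant |
|---|---|---|
| 8 | 62.8% | 24.6% |
| 9 | 70.6% | 37.1% |
| 10 | 76.5% | 47.2% |

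**Arm-by-period term.** This is a GEE on the two half-year indicators (saturated logit, robust standard errors, 6,000 simulated trials). For departure at month 6 it is significant in about 22% (30% versus 20%) or 66% (40% versus 20%) of trials. For departure at months 8, 9 and 10 (40% versus 20%) the figures are about 26%, 14% and 9%; repeat runs agreed to within about two percentage points.

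**Strictness.** Among irregular quarterly attenders in care all year, 1 − 0.748 = 25% fail the both-halves rule, against 5 × exp(−4) = 9% who fail the stated rule.

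**The case against.** The best defence is that an article condenses. Chart review is scheduled repeatedly, so interval coding of retention may sit in the full protocol or SAP, and a dichotomous variable can be a repeated one. Against this, the article does not leave the outcome open. It fixes one value over 12 months and then names a repeated-measures model for it in the same section. It remains true that no estimate is biased by the mismatch and that the logistic regression answers the question as defined.

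A second objection is that two or more visits in a year is explicit and computable, and that a spacing rule is a preference. The conflict does depend on reading *sustained* as lasting over the 12 months of coaching. Durable viral suppression, the primary outcome, gives separate evidence of persistence, although it does not measure care attendance.

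Third, the size comes from assumed inputs. In the month-6 scenario 30% of SOC but only 10% to 20% of MEI participants are never in care. That is a true benefit, and engagement is part of the aim, so 15% to 42% is not a false-positive rate. The figures also assume the planned 102 per arm. The article reports 36 enrolled in aim 2 with recruitment ongoing; at 18 per arm the same scenario gives about 8% to 13%. Both points stand.

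Finally, the half-year rule is stricter and still credits some people who leave after month 6. That also stands, which is why it should be added beside the stated outcome and not replace it.

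**Conclusion.** The concern holds. The mismatch between a single yearly value and a repeated-measures GEE follows from the text and needs no assumption. So does the fact that two early visits meet the definition. How much this matters depends on assumed visit rates and departure times: 26% to 80% of month-3 leavers and 59% to 98% of month-6 leavers count as retained. In the month-6 arm contrast, an arm difference is declared in about 15% to 42% of trials although all-year retention is equal. These figures illustrate the problem and do not predict this trial's result.

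The reach is limited to a secondary outcome. The logistic regression fits the outcome as defined, the time-by-arm term was not stated for retention, and durable viral suppression and the sample size are untouched. The plan should be corrected, but the trial's main question does not depend on it.

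**What to change.** Before outcomes are examined by arm:

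1. Keep the logistic regression on two or more visits, labelled as attendance over 12 months with no spacing requirement.
2. From the chart reviews that Table 2 schedules at 3, 6, 9 and 12 months, define two values per participant: at least one documented HIV care visit after randomization in months 0 to 6, and at least one in months 6 to 12. Use these in the GEE with arm, period and arm-by-period.
3. Report a visit in both halves by logistic regression beside item 1, as retention over the 12 months of coaching. Give estimates with confidence intervals for both. Do not infer fading because one is significant and the other is not.

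No new study visits are needed. The change needs care-visit dates from the chart reviews; the article does not say what is extracted, but an outcome of documented visits within 12 months already requires dated records.

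The costs are a stricter rule that irregular attenders fail more often, no minimum gap around month 6, partial credit for people who leave after month 6, and low power of the arm-by-period term when departure is late. The half-year measure reduces the problem without removing it.

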#### Coach-Based MEI for Youth at Risk for HIV

The third aim is to use an RCT to examine the efficacy of a mobile-enhanced coach-based intervention to achieve uptake of and adherence to PrEP and other preventive behaviors (eg, *protected* sex acts) among youth at elevated risk of HIV infection.

#### Aim 3

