##### Study Sample

This sample will be composed of YBLMSM or YBLTW recruited into aim 1, who test negative for HIV but are not currently on PrEP, and report either engaging in condomless anal intercourse or a prior history of a sexually transmitted infection. Additional eligibility includes no plan to relocate in the next 18 months; not enrolled in another PrEP behavioral intervention; and currently own or have access to a cell phone, private tablet, or laptop. Potential participants are provided information about the study and must consent to participate. We aim to recruit 225 YBLMSM or YBLTW at risk for HIV.

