##### Study Procedures

After enrollment, participants complete a baseline survey and are randomized (1:1) to 1 of 2 study arms: coached-based MEI or SOC. Randomization to the intervention arms is stratified by site; age group, to yield a balanced randomization between younger (aged 15-19 years) and older (aged 20-24 years) age groups; and the enrollment city. After each participant is identified, they are provided with their assigned treatment assignment.

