#### Sample Size Considerations

We aim to recruit up to 2000 YBLMSM and YBLTW to be screened for eligibility for aims 2 and 3. We conservatively estimate that 15.00% of the RDS recruited sample will be HIV-infected and not virally suppressed, given an HIV prevalence of 25% to 40% among YBLMSM and YBLTW across the sites and as many as 60% of HIV-infected YBLMSM are undiagnosed [4,9].

We expect a 15.0% loss to follow-up over 1 year in aim 2. Starting with n=240 will yield an effective sample size of 204 individuals in total, or 102 in each group, available for analysis in aim 2. A total estimate of n=200 will be enough to detect an average increase in the viral suppression proportion over the 3 follow-up visits of 16.0% from 24.0% assumed in the control arm to 40.0% in the coached-based MEI arm (odds ratio, OR 2.03), assuming a power of 85.0%. We expect a slightly greater loss to follow-up (20.0% loss to follow-up) in participants in aim 3. Starting with n=225 will yield an effective sample size of 180 individuals in total or 90 in each group. We estimate that a total of 180 participants (90 per group), and assuming a 15.0% average rate on PrEP in the control arm, we can detect an average increase of 14.0% to 29.0% (OR 2.31) with power 85.0%. Lost to follow-up estimates are based on the team’s prior work with this population.

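### The aim 3 primary and secondary outcomes are defined in PrEP users and PrEP nonusers, groups that form after randomization; this conflicts with the plan's own intention-to-treat statement, sample size and models

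*Protocol article*

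**What the plan says.** All references are to the protocol article.

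- **Primary outcome (Data Analysis, following Sample Size Considerations).** "The primary outcome for aim 3 is self-reported PrEP use over 12 months in PrEP users".
- **Analysis principle (same paragraph).** "The overall approach is based on an intention-to-treat analysis with treatment assignment" as the main explanatory variable in every model.
- **Secondary outcome (same paragraph).** Here the population is the complementary group: "the secondary outcome is self-reported condom use in PrEP nonusers".
- **Entry criterion (Aim 3, Study Sample).** Participants are youth "who test negative for HIV but are not currently on PrEP".
- **Allocation (Aim 3, Study Procedures).** They are "randomized (1:1) to 1 of 2 study arms: coached-based MEI or SOC".
- **Objective (Coach-Based MEI for Youth at Risk for HIV).** The intervention is tested for its ability "to achieve uptake of and adherence to PrEP and other preventive behaviors".
- **Sample size (Sample Size Considerations).** 225 enrolled, 20% loss, 180 analyzed, 90 per group, "assuming a 15.0% average rate on PrEP in the control arm", rising to 29% (OR 2.31) with 85% power.
- **Models (Data Analysis).** For uptake, "a survival model is used to examine whether intervention assignment is associated with time to PrEP use". A GEE then compares PrEP utilization and adherence over time by assigned arm. Neither model is said to be limited to users.

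**The concern.** No one is on PrEP at entry. Whether a participant later counts as a user or a nonuser is therefore decided after randomization, and it is the behavior that coaching is meant to shift. If the intervention works, the MEI users include people who would not have started under SOC, and the MEI nonusers have lost those same people. The arms are then no longer comparable within either group.

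Two things are at stake. The trial's headline question for aim 3 is whether coaching gets more youth onto PrEP, and an outcome read only among those who are on it cannot answer that. In addition, a difference or a null result within users or within nonusers could come from who entered the group rather than from any effect of coaching. As the text stands, a reader cannot tell whether aim 3 succeeds on PrEP use in everyone randomized or on use among starters, and these can disagree.

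**Working it through.** **1. The plan's own figures.** From Sample Size Considerations:
- Odds ratio: (0.29/0.71) / (0.15/0.85) = 2.31, as stated.
- Dropout: 225 × 0.80 = 180, or 90 per group, as stated.
- Power: a single comparison of 15% vs 29% with 90 per group (two-sided 0.05, pooled normal test; alpha and sidedness are my assumptions) gives 62%. Averaging over 3 visits with within-person correlation ρ multiplies the variance by (1 + 2ρ)/3. At ρ ≈ 0.37 this is 0.58, the effective size is 90/0.58 ≈ 155 per group, and power is about 85%. The 85% is therefore attainable, but it cannot be confirmed because ρ is not given.

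The sizing only makes sense for PrEP use in whole arms. A 15% control rate is a share of everyone in the SOC arm.

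**2. The passages side by side.**

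| Place | Population implied for PrEP use |
|---|---|
| Outcome definition | Users only |
| Intention-to-treat statement | All randomized |
| Sample size | All analyzed, 90 per group |
| Survival model and GEE | By assigned arm, no restriction to users |

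The outcome definition stands alone against the other three.

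**3. How many users there would be.** The 15% and 29% are average rates, so the number who are ever users depends on turnover. Assume 3 follow-up visits (the article names 3 for aim 2; the number for aim 3 is my assumption).
- Same people at every visit: 90 × 0.15 = 13.5 SOC and 90 × 0.29 = 26.1 MEI, total 39.6, about 40 of 180.
- Different people at every visit: 3 × 13.5 = 40.5 SOC and 3 × 26.1 = 78.3 MEI, total 118.8, about 119 of 180.

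**4. Power among users.** Assume a 14-point difference, 50% vs 64% (not from the documents), two-sided 0.05. Power = Φ[(0.14 − 1.96·SE0)/SE1], with SE0 from the pooled proportion 0.592 and SE1 unpooled.
- 13.5 vs 26.1: SE0 = 0.165, SE1 = 0.165, power = 13%.
- 40.5 vs 78.3: SE0 = 0.095, SE1 = 0.095, power = 31%.

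**5. Direction of the bias.** All behavioral rates here are assumed, and coaching has no effect on the behavior being compared.
- *Users.* Let 15% of each arm start PrEP regardless and a further 14% start only because of MEI. If the first group persists at 70% and the induced group at 40%, users compare at 70% SOC vs (0.15 × 0.70 + 0.14 × 0.40)/0.29 = 56% MEI. Swap the two rates and it is 40% vs (0.15 × 0.40 + 0.14 × 0.70)/0.29 = 54%.
- *Nonusers.* Let 40% of youth be one type and 60% the other, with only the first type starting PrEP. If the first type uses condoms at 60% and the second at 20%, nonusers compare at (0.25 × 0.6 + 0.6 × 0.2)/0.85 = 31.8% SOC vs (0.11 × 0.6 + 0.6 × 0.2)/0.71 = 26.2% MEI, an apparent harm of 5.6 points. Swap the condom rates and it is (0.25 × 0.2 + 0.6 × 0.6)/0.85 = 48.2% vs (0.11 × 0.2 + 0.6 × 0.6)/0.71 = 53.8%, an apparent benefit of 5.6 points.

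The bias is real in both groups, but its sign depends on who starts PrEP, which the documents do not tell us.

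**The case against.** The strongest reply is that the users clause is loose wording. The next sentence commits to intention to treat, the sizing uses whole arms, and the survival model and the GEE compare assigned arms without restriction. That stands in part: a reader might infer that the plan contains no uptake analysis, and that would be wrong. But the clause is the one that names the primary outcome. It is paired with a matching nonuser clause for the secondary, and nothing elsewhere gives the condom outcome an all-randomized version.

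A second reply is that use over 12 months among users means persistence or adherence, which is also part of the aim. That is a possible reading, and it is why one should not claim that the outcome would be near 100% by construction. Under this reading, though, the primary outcome omits uptake, the 15% vs 29% sizing belongs to a different endpoint, and the comparison is still among self-selected starters.

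A reader might also infer that MEI is bound to look harmful on condom use, or that power is 13%. Neither is supported. The sign reverses when one assumption is swapped, and 13% is the low end of a range that rests on assumed rates.

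Finally, the two PrEP models address different questions (time to uptake; utilization and adherence), and the choice of deciding test may sit in an analysis plan that is not shown. Having two models is therefore not a defect in itself.

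**Conclusion.** The point holds as an internal contradiction in the definition of the aim 3 outcomes. It follows from the entry criterion and the outcome text alone and does not depend on any power figure. As worded, neither between-arm contrast is protected by randomization, and the primary outcome cannot measure uptake.

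If the wording were carried out literally, the primary comparison would rest on roughly 40 to 119 of 180 participants, with about 13% to 31% power for the assumed 50% vs 64%, against the stated 85%. Those figures assume 3 visits, the plan's 15% and 29%, and two-sided 0.05. The direction of the selection bias cannot be determined from the documents. Because the defect lies in the population of a primary outcome, it must be corrected; the rest of the plan already points to the correction.

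**What to change.** Reword the outcome paragraph in Data Analysis:

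- **Primary:** self-reported PrEP use, yes or no at each follow-up visit over 12 months, in all randomized aim 3 participants. This matches the average rate used for the sample size.
- **Deciding test:** name one. The GEE contrast averaged over visits fits the sizing; time to PrEP use is also defensible. Keep the other as supportive.
- **Secondary:** define it in all randomized participants too, either as condom use or as sex acts protected by condom or PrEP. The second asks a somewhat different question, but protected sex acts are already in the aim. The choice belongs to the investigators.
- **Descriptive:** report adherence in users and condom use in nonusers, labelled as non-randomized comparisons.

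The cost is a wording amendment, with any analysis plan and registry entry checked for the same clause. The abstract reports 123 participants already in aim 3, so this is a change during enrollment and should be dated and made before any comparison by arm is seen. The surveys are already scheduled in both arms, so no new data or participants are needed.

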**Substance use**
Car, relax, alone, forget, friends, and trouble (CRAFFT) six-item substance use screen and a modified Time Line Followback assessing days of use of various substances [72,73]

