Going beyond the intention-to-treat approach, we will develop multivariate models stratified by age group (aged 15-19 years and 20-24 years) and include potential confounders and predictors such as prior exposure to case management and PrEP, sexual risk (low vs high), and other demographic variables. Additional models will be evaluated for possible dose-response relationships considering a measure of the level of engagement with the intervention and the frequency of app use. We will assess whether receiving coached-based MEI results in decreased substance use severity, by examining changes in mean CRAFFT scores (a measure of substance use severity) over time for the intervention group compared with the control group for each aim. CRAFFT scores will be treated as continuous dependent variables, and the models will adjust for intra-personal correlations between repeated measurements. Multivariate linear regression will be used to test for decreased severity at each follow-up visit, while controlling for identified confounders.

Modeling techniques have been selected based on the capacity to adequately handle the missingness of data. GEE models assume that the missingness is because of a missing at the random mechanism, which is a restrictive assumption. To address dropout, we use inverse probability weighting to relax this assumption of missing at random [92,93]. Other types of missing data will be handled using multiple imputations.

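### Aim 3 PrEP use and substance use in both aims rest on self-report in openly assigned arms, and no stated PrEP or substance-use analysis draws on the scheduled chart reviews or urine drug tests

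*Protocol article*

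**What the plan says.** In the protocol article's Data Analysis section, the aim 3 primary outcome is defined by participants' own account: it "is self-reported PrEP use over 12 months in PrEP users". The secondary outcome has the same source: "the secondary outcome is self-reported condom use in PrEP nonusers". The same section then models time to PrEP use with a survival model, and PrEP utilization and adherence with GEE. It names no other data source for either.

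For substance use, in both trials, the section says: "We will assess whether receiving coached-based MEI results in decreased substance use severity, by examining changes in mean CRAFFT scores". CRAFFT is a questionnaire. The study-measures textbox describes the substance-use content of the survey as a "six-item substance use screen and a modified Time Line Followback assessing days of use of various substances", so both instruments are self-report.

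Table 2 (Data Collection for Aims 2 and 3) has a row "Medical chart review (research staff only)", ticked at every visit from baseline to 18 months. It also has a row "Provide urine for drug testing", ticked at baseline, 3, 6 and 12 months.

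The article does not mention blinding. Aim 3 Study Procedures says that participants are given their assignment. The SOC and MEI Coach Intervention sections describe visibly different contact. The coached arm receives motivational interviewing, substance-use brief intervention and goal setting, with weekly check-ins. The control arm receives a short check-in with active listening and none of those techniques.

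**The concern.** The behaviors that the coach works on (starting and keeping up PrEP, condom use, cutting down substance use) are the ones the participant is later asked to report. In the control arm nobody sets goals on them. A participant who knows the arm and has agreed goals with a coach has a reason to report favorably that a control participant lacks. That error runs toward the intervention.

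Nothing in the stated analysis removes it. Intention-to-treat keeps the arms as randomized, GEE handles within-person correlation, and inverse probability weighting and multiple imputation address missing data. All of them take the reported value as correct. A positive aim 3 result, or a fall in CRAFFT score, could therefore partly or wholly reflect reporting, and the stated analyses offer no second source to compare it with.

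Aim 2 is treated differently in the same section: its primary outcome is a measured viral load, and its secondary outcome is retention based on documented visits.

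**Working it through.** **1. Which scheduled measurements reach which outcome (Data Analysis section against Table 2)**

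| Outcome | Source in the stated analysis | Other source in Table 2 | Used for this outcome? |
|---|---|---|---|
| Aim 2 viral suppression | blood viral load | – | – |
| Aim 2 retention in care | documented visits | chart review | evidently yes |
| Aim 3 PrEP use | self-report | chart review | not stated |
| Aim 3 condom use | self-report | none | – |
| Substance use, both aims | CRAFFT | urine drug test | not stated |

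**2. The plan's own aim 3 figures (Sample Size Considerations)**

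- Attrition: 225 × 0.80 = 180, or 90 per arm. Reproduces.
- Odds ratio for 15% against 29%: (0.29/0.71)/(0.15/0.85) = 2.31. Reproduces.
- Power: 90 per arm at a single time point gives 62% (two-sided 0.05). Averaging three visits with common correlation ρ multiplies the variance by (1 + 2ρ)/3, and the stated 85% is then reached at ρ of about 0.37. The article gives neither ρ nor the number of visits for aim 3, so 85% is attainable but cannot be confirmed. It does not decide this point.

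**3. Illustration of the size**

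From the article: 15% control rate, 90 analyzed per arm. Assumed: no true effect, a spurious excess d in the coached arm, three follow-up visits (stated for aim 2 only), two-sided 0.05, and ρ from 0 to 1.

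SE = √{[0.15 × 0.85 + p₁(1 − p₁)]/90 × (1 + 2ρ)/3}, with p₁ = 0.15 + d

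P(reject) = 1 − Φ(1.96 − d/SE) + Φ(−1.96 − d/SE)

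For d = 0.05 and ρ = 1: SE = √[(0.1275 + 0.1600)/90] = 0.0565, d/SE = 0.885, P = 0.141 + 0.002 = 0.143.

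For d = 0.10 and ρ = 1: SE = √[(0.1275 + 0.1875)/90] = 0.0592, d/SE = 1.690, P = 0.394.

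| ρ | d = 5 points | d = 10 points |
|---|---|---|
| 1 | 14% | 39% |
| 0.5 | 19% | 54% |
| 0.36 | 22% | 61% |
| 0.2 | 25% | 70% |
| 0 | 33% | 83% |

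**4. What d means in people**

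With 85% true non-users, a 5-point excess needs 0.05/0.85 = 5.9% of coached non-users to report use, and 10 points needs 0.10/0.85 = 11.8%. Reproducing the whole 14-point design effect would need 0.14/0.85 = 16.5%.

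**The case against.** **Charts are used.** A reader might infer that chart review enters no outcome at all. The text does not support that: aim 2 retention rests on documented visits and is modeled, and chart review is its evident source. The gap is confined to PrEP and substance use.

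**A condensed article may leave urine data to a fuller plan.** This stands in part. Substance use is neither a primary nor a secondary outcome here, and silence on how a collected laboratory result will be analyzed is common in an article. The urine part is therefore a suggestion. The PrEP part is different, because the article itself fixes the primary outcome as self-report.

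**The objective data may not answer the question.** A reader might infer that charts and urine would settle it. They would not. Table 2 does not say what is abstracted or whose charts are reached, and a prescription is not use. Coaching includes navigation, so chart capture could itself differ by arm. Urine shows recent use, while the stated target is severity.

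**Reports may not go to the coach.** The abstract describes a web-based survey, and the aim 1 Study Activities section says that data are tracked by study ID only. Both weaken the pressure to please but do not remove it, since participants still know their arm and their goals.

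**The size is hypothetical.** This stands. Five points on a 15% base is a one-third inflation confined to one arm, and the article offers no figure for it.

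**Conclusion.** The concern holds in limited form. The aim 3 primary outcome and the substance-use comparison in both aims are self-reported, arm assignment is open in practice (an inference from the procedures, not a stated design feature), and only one arm is coached on the reported behaviors. No stated PrEP or substance-use analysis draws on the scheduled chart reviews or urine tests.

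The rejection rates of about 14% to 33% at 5 points and 39% to 83% at 10 points depend on the assumed excess, the three visits and the correlation. They show that modest differential reporting could matter at this sample size. They do not measure the bias in this trial or show that any exists.

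A reader might also infer that a chart-based outcome should replace the self-reported primary. The material does not support that: it would exchange reporting error for incomplete and possibly arm-dependent capture. The point is a worthwhile, low-cost improvement and not a flaw that invalidates the design.

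**What to change.** 1. Keep self-reported PrEP use as the aim 3 primary outcome. Prespecify, as its key sensitivity analysis, PrEP use corroborated by a PrEP prescription found in the chart review, with the same arm comparison.
2. Add urine drug-screen positivity at 3, 6 and 12 months as a supporting substance-use outcome beside CRAFFT in both trials, analyzed by GEE with adjustment for the baseline urine result. State that it reflects recent use and not severity.
3. Say in advance how disagreement will be read: the chart and urine results can support or weaken the self-report findings but do not override them.

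**Cost.** Analysis-plan wording and one chart-abstraction field, with no new visits or samples. The chart-corroborated rate will be lower than the self-reported rate because charts miss outside providers. That loss may differ by arm, so the report should say which providers' charts were reached, by arm.
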